# Live birth after letrozole as an adjunct to follicle-stimulating hormone versus follicle-stimulating hormone alone for ovarian stimulation in in vitro fertilisation cycles—study protocol for a randomised controlled trial

**DOI:** 10.1186/s13063-022-06185-0

**Published:** 2022-04-01

**Keywords:** Letrozole, Estradiol, In vitro fertilisation, Fresh embryo transfer, Live birth rate, Randomised controlled trial

## Abstract

**Introduction:**

In vitro fertilisation (IVF) is an effective infertility treatment but the live birth rate remains unsatisfactory. Ovarian stimulation by follicle-stimulating hormone (FSH) is routinely used in IVF and the resulting high serum estradiol levels may impair oocyte/embryo quality and endometrial receptivity. Letrozole, an aromatase inhibitor, can reduce serum estradiol levels following ovarian stimulation. We aim to test the hypothesis that co-treatment with letrozole reduces supraphysiological serum estradiol levels and improves endometrial receptivity, leading to a higher live birth rate of IVF. We are conducting a randomised controlled trial (RCT) to evaluate whether letrozole as an adjunct to FSH in IVF is superior to FSH alone in the live birth rate of fresh embryo transfer.

**Methods/design:**

This is an open-label randomised controlled superiority trial being performed in two assisted reproduction centres in China. Infertile women who have antral follicle count (AFC) before ovarian stimulation or on day 5 of ovarian stimulation ≥15 are randomly allocated in a 1:1 ratio to receive either letrozole and FSH or FSH alone in a GnRH antagonist protocol. Recruited women follow the standard operating procedures of the two centres. The primary outcome is the live birth rate of the fresh embryo transfer. Stimulation parameters, maternal side effects and obstetric and perinatal complications are secondary outcomes. The planned sample size is 900, i.e. 450 per group.

**Discussion:**

The present study is the first multicentre randomised study to compare the live birth rate of the fresh embryo transfer following ovarian stimulation by letrozole and FSH versus FSH alone in women with anticipated high ovarian responses.

**Trial registration:**

ClinicalTrials.gov NCT02912988. Registered on September 23, 2016. This trial protocol is version 2.0.

## Background

Despite improvements in ovarian stimulation regimens and laboratory techniques, the live birth rate of in vitro fertilisation (IVF) remains unsatisfactory [1]. Ovarian stimulation is used in the great majority of IVF cycles and may lead to high serum estradiol (E2) levels with adverse effects on oocyte/embryo quality and endometrial receptivity [2–6].

High serum E2 levels have been implicated in reducing oocyte quality and increasing embryo aneuploidy rates [4–7]. The impact of supraphysiological E2 levels on endometrial receptivity includes disruption of endometrial gene expression [8], cytokine profiles [9] and histological markers of endometrial receptivity [10, 11]. High serum E2 level during ovarian stimulation is associated with an increased risk of small for gestational age and preeclampsia in singleton pregnancies after IVF [12].

Letrozole, a third-generation aromatase inhibitor, reduces the intraovarian aromatisation of androgens to oestrogens. It is now the first-line drug treatment for ovulation induction in women with polycystic ovary syndrome (PCOS) [13] and is routinely used as a co-treatment during ovarian stimulation in women with hormone-sensitive cancers such as breast cancer to reduce the risk of recurrence associated with high serum E2 levels during ovarian stimulation [14]. Peak serum E2 levels were significantly lower in the letrozole cohort [15–17].

Letrozole has been used for endometrial preparation in frozen embryo transfer (FET) in women both with anovulation caused by PCOS and with regular cycles. Retrospective studies [18–20] showed that the ongoing pregnancy rate or live birth rate of FET in letrozole-induced cycles was significantly higher than that in hormonal cycles of women with polycystic ovary syndrome or ovulation disorders. A large retrospective cohort study [21] reported the pregnancy outcomes of 110,722 FET cycles replacing a single embryo in letrozole, natural or hormonal cycles. The rates of clinical pregnancy, ongoing clinical pregnancy and live birth were significantly higher, while the rate of miscarriage was significantly lower in the letrozole group compared with the natural and hormone replacement therapy (HRT) groups.

The above studies indicate that adding letrozole to ovarian stimulation may improve endometrial receptivity by reducing supraphysiological serum E2 levels and have a direct effect on endometrial receptivity. By combining sufficient FSH stimulation to produce adequate numbers of oocytes, with a simple oral adjuvant therapy aimed at preventing excessive estradiol levels, the resultant stimulation protocol may provide a ‘best of both worlds’ solution, in which adequate numbers of oocytes are obtained, but not at the cost of detrimental impacts on oocyte, embryo or endometrial quality.

The aim of this multicentre randomised controlled trial is to test the hypothesis that co-treatment with letrozole leads to a higher live birth rate of fresh embryo transfer.

### Study setting

This is an open-label randomised controlled superiority trial being performed in the Department of Obstetrics & Gynaecology, The University of Hong Kong, and the Centre for Reproductive Medicine, Department of Obstetrics and Gynecology, Peking University Third Hospital. Written informed consent was obtained from all participants before participation in the study.

## Methods/design

### Study design

Eligible women will be given information about the study during their first consultation. All recruited women provided written informed consent before participation. The trial was approved by the institutional review board of the University of Hong Kong/Hospital Authority Hong Kong West Cluster (UW16-014) and the Ethics Committee of Peking University Third Hospital (2016sz-066). The study was registered on Clinicaltrials.gov (NCT02912988).

The enrollment, interventions and evaluation during the study process are shown in Table 1. Figure 1 indicates a flowchart showing registration, allocation, intervention and follow-up of participants.

**Table 1 Tab1:** Schedule of enrollment, interventions and assessments

	Study period							
	Enrollment	Allocation		Post-allocation				Close-out
Content	Screening and baseline assessment	Ovarian stimulation and randomisation	Oocyte retrieval	Assessment of embryo	Embryo transfer	Evaluation of pregnancy	Follow-up of pregnancy	
Time point	T0 −1 month	T1 0 month	T2 8–12 days	T3 1–3–5 days after retrieval	T4 2–5 days	T5 1 month	T6 3–10 months	T7 12 months
Enrollment								
Eligibility screen	×	×						
Informed consent		×						
Allocation		×						
Interventions								
Letrozole and FSH		×						
FSH alone		×						
Assessments								
Baseline data	×							
Laboratory tests	×	×	×			×	×	×
Fertilisation check				×				
Embryo quality				×	×			
Pregnancy tests						×		
Pregnancy outcomes							×	×
Foetus information							×	×
Neonate information							×	×
Safety assessment		×	×		×	×	×	×

**Fig. 1 Fig1:**
[figure not shown]
Flowchart of clinical RCT study: letrozole + FSH vs FSH alone for ovarian stimulation in IVF

### Recruitment

Infertile women undergoing IVF treatment at the Department of Obstetrics & Gynaecology, the University of Hong Kong, and the Centre for Reproductive Medicine, Department of Obstetrics and Gynecology, Peking University Third Hospital, will be screened for eligibility. Eligible women will be counselled about the trial on the first day attending the centres for ovarian stimulation. Written informed consent will be obtained before joining the trial. Participants can decline to join the study at any time without any consequences for their clinical treatments.

### Eligibility criteria

#### Inclusion criteria

Women less than 42 years of ageHaving a medical indication for IVF treatmentTotal antral follicle count (AFC) on pelvic scanning before ovarian stimulation or on day 5 of stimulation ≥15Written informed consent obtained

#### Exclusion criteria

Women using donor oocytesWomen undergoing preimplantation genetic testingWomen with abnormal uterine cavity shown on hysterosalpingogram or saline infusion sonogramWomen with hydrosalpinges shown on scanning and not correctedHaving previously documented poor response, i.e. ≤3 oocytes to ovarian stimulation using at least FSH 225 IU daily

### Randomisation and allocation concealment

Recruited women will be randomly allocated in a 1:1 ratio to the letrozole group or the control group according to a computer-generated randomisation list put in opaque sealed envelopes which are open consecutively for eligible participants after screening. Both investigators and participants are aware of the allocation of the intervention. The biostatistician performing the data analysis will be blinded to the group allocation.

### Interventions

A gonadotropin-releasing hormone (GnRH) antagonist regimen is used. Human menopausal gonadotropin (HMG; Menopur, Ferring Pharmaceuticals, Saint-Preix, Switzerland) or recombinant human follicle-stimulating hormone (FSH; Gonal-F, Merck Serono, Geneva, Switzerland) is administered at a dose of 150 to 225 IU per day based on body mass index and previous ovarian response on day 2–4 of the menstrual cycle, at the discretion of the physicians. Transvaginal scanning, serum luteinizing hormone (LH), oestrogen (E2) and progesterone (P4) will be performed regularly to monitor ovarian response. HMG or FSH doses will be adjusted according to ovarian responses.

GnRH antagonist 0.25 mg (Cetrotide, Merck Serono, Darmstadt, Germany, or Orgalutran, Merck Sharp & Dohme Ltd.) is started from day 5 of stimulation until the day of the trigger. When three or more follicles reach a diameter ≥ 17 mm, 250μg of rhCG (Ovidrel; Serono, Aubonne, Germany) or triptorelin 0.2 mg (Diphereline, Ipsen Beaufour) is to be given for final maturation. Oocyte retrieval is performed around 36 h after the trigger.

In the letrozole group, letrozole (Letroz, Sun Pharmaceuticals, Mumbai, India) 2.5 mg daily is started from day 5 of stimulation until the day before the trigger. The control group will not receive letrozole.

When the serum estradiol level on the day of hCG administration or before the day was ≥20000 pmol/L, 0.2 mg of triptorelin (Ferring International Center, Saint-Prex, Switzerland) will be given for agonist trigger. When the serum estradiol level on the day of hCG administration or before the day was 15,000–20,000 pmol/L, 0.2 mg of triptorelin (Ferring International Center, Saint-Prex, Switzerland) and 2000 IU of hCG (Livzon, Zhuhai, China) or 125 mg of recombinant hCG (Ovidrel; Merck Serono) will be given.

The freeze-all strategy to prevent ovarian hyperstimulation syndrome (OHSS) is advised in women with (1) E2 on HCG day ≥15,000 pmol/L, (2) retrieved oocyte number ≥ 20, and (3) E2 on HCG day ≥10,000 pmol/L and retrieved oocyte number ≥ 15.

### Assessment of fertilisation and embryo culture

Oocytes are cultured in Human Tubal Fluid medium and incubated in a humidified 37 °C incubator with 5% CO2, after oocyte retrieval immediately. The fertilisation method will be selected according to the parameters of the semen analysis.

Fertilisation will be considered normal when two pronuclei are present between 16 and 18 h after conventional insemination or intracytoplasmic sperm injection (ICSI). All zygotes will be cultured in a cleavage medium (G-1plus, Vitrolife, USA) for further 48–52 h after fertilisation. Cleavage stage embryos will be assessed according to the developmental stage and degree of cytoplasmic fragmentation.

### Embryo transfer and luteal support

Fresh embryo transfer or elective freezing of all embryos will be decided by physicians according to the conditions of women. All embryos will be cryopreserved without fresh transfer when the women are at risk of OHSS, have elevated serum progesterone level on the trigger day (> 1.5 ng/L or > 5 nmol/L) or had endometrial polyps or fluid in the uterine cavity. To reduce the risk of multiple pregnancies, up to two embryos will be transferred on day 2/3 and one blastocyst will be replaced on day 5. Excess cleavage stage embryos will be vitrified or further cultured to the blastocyst stage while excess blastocyst will be vitrified accordingly.

In women with fresh embryo transfer, the luteal phase is supported with vaginal progesterone gel (Crinone, Merck Serono) at a dose of 90 mg daily or oral progesterone (Duphaston, Abbott) at a dose of 10 mg three times daily from the day of oocyte retrieval until the day of serum or urine hCG test.

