#### Secondary outcomes

Secondary outcomes include pregnancy outcomes, maternal safety and obstetric and perinatal complications. Detailed information is provided in Table 2. Maternal safety is an important part of the secondary outcomes. The incidence of OHSS is the key indicator of maternal safety and is classified as mild, moderate or severe according to the RCOG guideline [22, 23]

**Table 2 Tab2:** Secondary outcomes and related definition

Secondary outcomes	Definition
Clinical and laboratory outcomes	
Total amount of FSH	Total amount of FSH used for ovarian stimulation
Number of follicles > 12 mm	The number of follicles > 12 mm measured by transvaginal ultrasound on the day of the trigger or the day before
Number of oocytes obtained	Number of oocytes obtained during oocyte retrieval
Number of embryos obtained	Number and quality of embryos obtained
Proportion of good-quality embryos	Embryos with 4 cells and < 25% fragmentation on day 2 or with ≥6 cells and ≤ 10% fragmentation on day 3, the proportion of oocytes resulting in top quality day 2 (or day 3) embryos according to validated morphological criteria
Oocyte fertilisation rate	The number of zygotes with 2PN over the number of mature oocytes for ICSI or over the number of oocytes for conventional insemination
Endometrial thickness	Endometrial thickness measured by transvaginal ultrasound on the day of the trigger or the day before
Serum E2 level	Serum E2 level on the day of the trigger or the day before
Serum P level	Serum P level on the day of the trigger or the day before
Serum testosterone level	Serum testosterone level on the day of the trigger or the day before
Follicular fluid E2 level	E2 level in the follicular fluid
Follicular fluid testosterone level	Testosterone level in the follicular fluid
Follicular fluid inhibin B level	Inhibin B level in the follicular fluid
Follicular fluid AMH level	AMH level in the follicular fluid
Pregnancy outcomes	
Miscarriage	Spontaneous loss of an intrauterine pregnancy before 20 completed weeks of gestational age
Clinical pregnancy	Presence of one or more intrauterine gestational sacs at 6 weeks of gestation
Ongoing pregnancy	Presence of one or more gestational sacs and foetal heartbeat after 12 weeks of gestation
Maternal safety outcomes	

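### Two units in the treatment rules are misprinted: the progesterone freeze-all limit (ng/L, where only ng/mL fits) and the dual-trigger recombinant hCG dose (mg, where μg is evidently meant)

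*Protocol article*

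**What the plan says.** **Progesterone limit.** Under Embryo transfer and luteal support, the protocol article lists the conditions that rule out a fresh transfer. It begins "All embryos will be cryopreserved without fresh transfer when the women are at risk of OHSS" and goes on to women who "have elevated serum progesterone level on the trigger day (> 1.5 ng/L or > 5 nmol/L"). The two values are given as the same threshold in mass and molar units. Serum progesterone is also mentioned under Interventions (monitoring) and in Table 2 ("Serum P level on the day of the trigger or the day before"), each time without a unit.

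**Recombinant hCG dose.** Under Interventions, the standard trigger is "250μg of rhCG" (Ovidrel), with triptorelin as the alternative. A second rule covers high estradiol: "When the serum estradiol level on the day of hCG administration or before the day was 15,000–20,000 pmol/L", triptorelin is combined with either 2000 IU of hCG or recombinant hCG, and for the latter the text reads "125 mg of recombinant hCG (Ovidrel; Merck Serono) will be given". The product is again Ovidrel.

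**Related rule.** The same section says that freezing all embryos "is advised in women with (1) E2 on HCG day ≥15,000 pmol/L", followed by two further criteria based on oocyte number, alone or combined with estradiol.

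**The concern.** A threshold stated in two units must be the same quantity in both. Here the mass figure and the molar figure cannot both be right. A woman whose trigger-day progesterone lies anywhere between about 0.005 and 5 nmol/L would have all embryos frozen under one printed limit and could have a fresh transfer under the other. Because the primary outcome is live birth following the fresh transfer, this limit is one of the rules that decide who can contribute a success.

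The hCG figure is a different kind of slip. An adjunct dose in a combined trigger should not exceed the full dose used alone, least of all in women whose estradiol is high enough for the protocol to advise freezing embryos to prevent ovarian hyperstimulation. What is at stake is a dosing error in a published regimen that others may copy. It has little route to the primary outcome, since most of these women are already advised against a fresh transfer.

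**Working it through.** **Inputs**

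- From Embryo transfer and luteal support: 1.5 ng/L, paired with 5 nmol/L.
- From Interventions: full trigger 250 μg; dual-trigger dose printed as 125 mg, same product; dual-trigger estradiol band 15,000–20,000 pmol/L; first freeze-all criterion from 15,000 pmol/L.
- Assumption, not in the article: the molar mass of progesterone is about 314.5 g/mol. This is a physical constant; a range of 310 to 320 g/mol is shown.

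**Progesterone**

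Conversion: nmol/L = (ng/L) ÷ (molar mass in g/mol).

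1. As printed: 1.5 ÷ 314.5 = 0.00477 nmol/L. Relative to the paired value: 0.00477 ÷ 5 = 0.095%. The printed equivalence is not reproduced.
2. In the other direction: 5 × 314.5 = 1,572.5 ng/L, and 1,572.5 ÷ 1.5 = 1,048. The pair is about 1,048-fold apart.
3. Sensitivity to the constant: at 310 g/mol, 1,550 ÷ 1.5 = 1,033; at 320 g/mol, 1,600 ÷ 1.5 = 1,067.
4. Molar mass needed for the printed pair to agree: 1.5 ÷ 5 = 0.3 g/mol, which is impossible. If the unit is ng/mL, the pair implies 1,500 ÷ 5 = 300 g/mol, close to the true value.
5. With ng/mL: 1.5 ng/mL = 1,500 ng/L, and 1,500 ÷ 314.5 = 4.77 nmol/L (4.84 at 310; 4.69 at 320). Each rounds to the printed 5 nmol/L.

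Reading the two figures as separate criteria does not help. Any woman above 5 nmol/L is already far above 1.5 ng/L, so the molar limit would be redundant.

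**Recombinant hCG**

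1. As printed: 125 mg = 125,000 μg, and 125,000 ÷ 250 = 500 times the full dose.
2. With μg: 125 ÷ 250 = 0.5, half the full dose, which is plausible for an adjunct to triptorelin.

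**Route to the primary outcome for the hCG slip**

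The dual-trigger band starts at 15,000 pmol/L, the same value at which freeze-all is advised. The overlap is not exact: the trigger rule uses estradiol on the day of hCG or before it, while the freeze-all criterion uses the hCG day only and is advice. Women in the band are therefore largely, not always, advised against a fresh transfer.

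**The case against.** The strongest reply is that neither slip could mislead anyone who runs the trial. The correct 5 nmol/L stands in the same parenthesis, and the estradiol thresholds are also molar, so the molar figure is the natural one to use. A literal 0.005 nmol/L limit is hard to square with a trial built on fresh transfers, whose 20% dropout allowance names cancelled transfers as an example. A 125 mg dose is implausible beside 250 μg of the same product and the 2000 IU alternative. Physicians decide between transfer and freezing, and the abstract states that "Recruited women follow the standard operating procedures of the two centres". The full protocol is not shown and may carry the right units. With 890 of 900 women already recruited, little in the conduct of the trial could still change.

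Most of this stands, and it bounds the consequence: no effect on the trial's conduct or results is shown. It does not make the printed units right. A reader has to recognise the error and choose the correct figure, and for the hCG dose no correct value is printed at all. That 125 μg was meant is an inference, though a strong one. A fault in reading the text from the file cannot be fully excluded for the dose, but the microgram symbol came through correctly in the same section. Such a symbol fault would not explain litres in place of millilitres.

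**Conclusion.** The concern holds. Both units are wrong as printed and nothing elsewhere in the article corrects them. The progesterone pair is inconsistent by a factor of about 1,048 (1,033 to 1,067 over the assumed molar-mass range), and no credible value of that constant reconciles it. The recombinant hCG dose is 500 times the article's own full dose.

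The point is minor. One slip lies in an operative threshold for fresh transfer and the other in a treatment dose, so both deserve correction. But sample size and primary analysis are untouched, and nothing in the article shows that either misprinted value was used. The conclusion rests on the molar mass of progesterone and, for the dose, on the inference that half the full trigger was intended. Whether the full protocol carries the same slips is unknown.

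**What to change.** Check both values against the two centres' operating procedures and the full protocol. Then publish a short correction:

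- Embryo transfer and luteal support: give the progesterone limit as > 1.5 ng/mL (about 5 nmol/L).
- Interventions, dual trigger: give the recombinant hCG dose as 125 μg.

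If the full protocol has the same units, correct it too. The cost is one brief notice, with no additional patients and no change to the sample size or the primary analysis.

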### Follow-up

Transvaginal ultrasonography will be performed 2 weeks after a positive serum or urine pregnancy test to confirm intrauterine pregnancy. Scanning will be repeated later to confirm ongoing pregnancy, which is defined as a viable pregnancy with a foetal heartbeat at 10–12 weeks. Information regarding the outcome of the pregnancy and obstetrical and perinatal complications will be obtained through a review of obstetrical medical records and neonatal medical records. The live birth is defined by the live foetus in the uterine after 20 weeks of gestation.

We will collect the following information within 6 weeks after delivery, including antenatal information (pregnancy complications and foetal information), delivery information (gestational age, mode of delivery, placental weight and birth complications) and newborn information (foetal sex, birth weight and birth defects).

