### Measurement of outcomes

#### Primary outcome

The primary outcome is the live birth rate after 20 weeks of gestation following the fresh transfer.

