OHSS	It is classified as mild, moderate or severe according to the degree of abdominal distention, ovarian enlargement and respiratory haemodynamic, and metabolic complications. Diagnosed by ultrasound, blood testing and physical examination according to the RCOG Guideline
Ectopic pregnancy	A pregnancy outside the uterine cavity, diagnosed by ultrasound, surgical visualisation or histopathology
Obstetric and perinatal complications	
Hypertensive disorders of pregnancy	Including pregnancy-induced hypertension, preeclampsia and eclampsia
Antepartum haemorrhage	Including placenta previa, placenta accreta and unexplained
Multiple pregnancies	Pregnancy with more than one foetus
Birth weight	Including low birth weight (weight < 2500 g at birth), very low birth weight (< 1500 g at birth), high birth weight (> 4000 g at birth) and very high birth weight (> 4500 g at birth)
Small for gestational age	Birth weight less than the 10th centile for the sex-specific birth weight for a given gestational age reference
Preterm delivery	Birth of a foetus delivered after 28 and before 37 completed weeks of gestational age
Congenital anomaly	Structural or functional disorders that occur during intrauterine life and can be identified prenatally, at birth or later in life, including trisomy 21 syndrome, neural tube defect, congenital heart disease, cleft lip, excessive numbers of fingers or toes and hydrocephalus
Perinatal mortality	Foetal or neonatal death occurring during late pregnancy (at 28 completed weeks of gestational age and later), during childbirth, or up to seven completed days after birth

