### Safety reporting

Adverse events (AE) are defined as any undesirable experience occurring to a subject during the trial. A serious adverse event (SAE) is any untoward medical event that results in death, is life-threatening (at the time of the event), requires hospitalisation or prolongation of existing inpatients’ hospitalisation, results in persistent or significant disability or incapacity, is a congenital anomaly or birth defect and is a new event of the trial likely to affect the safety of the subjects, such as an unexpected outcome of an adverse reaction.

SAE in this study includes moderate/severe OHSS, intraperitoneal haemorrhage or ovarian torsion after oocyte retrieval, ectopic pregnancy, severe preeclampsia, pregnancy complications leading to hospitalisation, stillbirth, birth defects and other serious medical events judged by researchers to meet the criteria of SAE.

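### As worded, the primary outcome counts a foetus alive in utero beyond 20 weeks as a live birth, with no delivery or live-born infant required

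*Protocol article*

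**What the plan says.** The protocol article describes the primary outcome in two places.

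- Follow-up: "The live birth is defined by the live foetus in the uterine after 20 weeks of gestation".
- Primary outcome: "The primary outcome is the live birth rate after 20 weeks of gestation following the fresh transfer".

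No other definition of live birth appears. The neighbouring outcomes are:

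- Miscarriage (Table 2): "Spontaneous loss of an intrauterine pregnancy before 20 completed weeks of gestational age".
- Preterm delivery (Table 2): "Birth of a foetus delivered after 28 and before 37 completed weeks of gestational age".
- Perinatal mortality (Table 2) begins with "Foetal or neonatal death occurring during late pregnancy (at 28 completed weeks of gestational age and later" and runs to seven days after birth.
- Ongoing pregnancy has two windows. Follow-up has "ongoing pregnancy, which is defined as a viable pregnancy with a foetal heartbeat at 10–12 weeks"; Table 2 has "Presence of one or more gestational sacs and foetal heartbeat after 12 weeks of gestation".
- The serious adverse events in Safety reporting include "pregnancy complications leading to hospitalisation, stillbirth, birth defects".

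Follow-up also says that pregnancy outcomes come from obstetric and neonatal records, and that delivery and newborn details are collected up to six weeks postpartum.

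**The concern.** A live birth is something that happens at delivery. The definition instead describes the state of a pregnancy some time after 20 weeks. An analyst who coded the primary outcome from that sentence would record a success for a woman whose foetus was alive in utero beyond 20 weeks and was later stillborn. The same woman would appear in the safety tables with a serious adverse event.

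The title, the aim at the end of the Background and the sample-size premise all refer to live birth, and the Discussion presents that choice of endpoint as a strength. If the literal definition were applied, the reported rate would be somewhat too high. Any difference between arms in loss after 20 weeks would also be left out of the primary comparison, whichever arm it favoured.

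**Working it through.** **1. Does any other text override the definition?** The Primary outcome sentence, read alone, could mean a birth occurring beyond 20 weeks. It does not say so, and it does not define live birth. Follow-up does define it, and places the foetus in the uterus. The explicit definition therefore governs.

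**2. What event is counted?** Three outcomes side by side:

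| Outcome | Event as written | Delivery needed? |
|---|---|---|
| Ongoing pregnancy | heartbeat at 10-12 weeks (Follow-up) or after 12 weeks (Table 2) | no |
| Live birth (primary) | foetus alive in utero beyond 20 weeks | no |
| Live birth in the ordinary sense | live-born infant delivered | yes |

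As written, the primary outcome is a viable-pregnancy milestone, later than the protocol's own ongoing pregnancy and short of birth.

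**3. The plan's own figure.** Inputs from Sample size calculation: 35% versus 45%, one-sided 2.5%, 80% power. With pooled variance and no continuity correction:

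n = [1.960 × √(2 × 0.40 × 0.60) + 0.842 × √(0.35 × 0.65 + 0.45 × 0.55)]² / 0.10² = 375.6, rounded up to 376 per arm, 752 in total.

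This matches the plan.

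**4. Women misclassified.** The documents give no rate of loss between 20 weeks and birth. Assume a rate L of 1-3%, and take 35% and 45% as the rates of a foetus alive at 20 weeks. The number misclassified per arm is n × rate × L.

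| Base per arm | Control (35%) | Letrozole (45%) |
|---|---|---|
| 376 | 131.6 × L = 1.3 to 3.9 | 169.2 × L = 1.7 to 5.1 |
| 450 | 157.5 × L = 1.6 to 4.7 | 202.5 × L = 2.0 to 6.1 |

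The base of 376 is the planned number before the dropout allowance; 450 is the number to be recruited. In percentage points of the rate, the range is 35 × 0.01 = 0.35 to 45 × 0.03 = 1.35.

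**5. Effect on the treatment difference.**

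- Equal loss: 10 × (1 − L) = 9.9 points at 1%, 9.8 at 2% and 9.7 at 3%.
- Unequal loss, 1% control and 3% letrozole: 45 × 0.97 − 35 × 0.99 = 43.65 − 34.65 = 9.0 points.
- Unequal loss, 3% control and 1% letrozole: 45 × 0.99 − 35 × 0.97 = 44.55 − 33.95 = 10.6 points.

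**6. Effect on sample size.** If 35% and 45% were meant as true live birth rates, 376 per arm is unaffected. If they were 20-week rates, equal loss of 1%, 2% or 3% raises the requirement for live birth to 382, 389 or 395 per arm.

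**7. Where late losses are recorded.** Miscarriage ends at 20 completed weeks and perinatal mortality starts at 28. A loss at 20-27 weeks is in neither, and the preterm delivery definition also leaves out births in that window. Stillbirth is reportable as a serious adverse event, with no lower gestational limit stated.

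**The case against.** The best defence is that the sentence is a drafting error. It is ungrammatical and contradicts the term it defines. The Primary outcome wording can be read as birth beyond 20 weeks. Delivery mode, gestational age and newborn data are collected, Table 1 schedules neonatal information to 12 months, and data collection runs to February 2023, ten months after recruitment is due to end. All of this suggests that real births were meant. That stands as a likely explanation, but not as a reason to leave the text alone: it is the only definition of the primary endpoint.

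The defence is right about several stronger readings that a reader might infer:

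- *The trial measures ongoing pregnancy.* The protocol's ongoing pregnancy is at 10-12 weeks or after 12 weeks. The literal primary outcome is a different and later milestone.
- *Late losses go unrecorded.* Deaths from 28 weeks fall under perinatal mortality, and stillbirth is reported as a serious adverse event. The gap is limited to the named secondary outcomes at 20-27 weeks.
- *Letrozole gives particular cause for concern about late loss.* Nothing in the document supports this. The only loss result it cites is a lower miscarriage rate with letrozole, in frozen-transfer cycles.
- *The 28-week thresholds are wrong.* Preterm delivery and perinatal mortality use 28 weeks consistently, and the secondary outcomes are declared exploratory. Moving the thresholds would be a preference.

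**Conclusion.** The point holds for the definition as worded. The only stated definition of the primary outcome requires no birth, and applied literally it would count a later foetal death or stillbirth as a success. It matters because it concerns the primary endpoint, not because a large bias is expected.

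Under the assumed 1-3% loss after 20 weeks, about 1-5 women per arm (on 376) or 2-6 (on 450) would be misclassified, and a 10-point difference would shrink to 9.7-9.9 points if loss is equal. The illustrative unequal cases give 9.0 and 10.6 points. These figures rest on the assumed loss rates and on applying the planned 35% and 45% to every woman in the base. The document does not show that the investigators intend to score the outcome literally.

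Two minor points go with it: the conflicting windows for ongoing pregnancy, and the 20-27 week gap between the miscarriage and perinatal mortality definitions.

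**What to change.** Replace the definition in Follow-up with: delivery of at least one live-born infant at or after 20 completed weeks of gestation, following the fresh transfer and ascertained from the delivery record. Use the same words under Primary outcome. Choose one window for ongoing pregnancy and use it in both Follow-up and Table 2. Add a note on how losses at 20-27 weeks will be reported, for example from the delivery and serious adverse event records; the 28-week definitions need not change.

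The cost is wording. The necessary records are already being collected, and 376 per arm is unchanged if 35% and 45% were meant as live birth rates. The reported rate may fall slightly. Because the trial is open-label and 890 of 900 women had been recruited at the time of writing, the correction should be dated and made before the outcome data are analysed.
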